## Abstract

**Background:**

The academic development and widespread adoption of meditation practices for well-being and therapy have predominantly focused on secularised adaptations of Buddhist and Hindu techniques. This study aims to expand the field by investigating Christian and Islamic meditation that emphasize the spiritual significance of the heart through elements of visualisation and recitation. It compares the effects of spiritual heart-centred meditation with mindfulness meditation and a waitlist control, focusing on dimensions of social functioning, psychophysiology, cognition, and mental health.

**Method:**

This study employs a stratified 3-arm randomised controlled method with mixed-method repeated measures across three assessment time points: before intervention (T1), after an 8-week intervention (T2), and at a 3-month follow up (T3). The three conditions include spiritual meditation (either Christian or Islamic), mindfulness meditation (Mindfulness-Based Stress Reduction – MBSR), and a waitlist. Participants will be stratified into Christian and Muslim samples and randomly allocated to the spiritual meditation, MBSR, or waitlist control conditions. Importantly, participants assigned to the spiritual meditation condition will be matched to the spiritual meditation program corresponding to their religion. The intervention will be administered through a mobile phone app with daily 20-minute guided meditation sessions for eight weeks. Primary outcomes pertain to the domain of interpersonal functioning, focusing on prosociality, forgiveness, empathy, and perspective taking. Secondary outcomes include physiology: pain tolerance, pain intensity, stress reactivity assessed via heart rate (HR) and heart rate variability (HRV), psychophysiological reactivity associated with a forgiveness task as measured through HR and HRV, attention (alerting, orienting, and executive attention networks), and mental health (stress, depression, anxiety, subjective well-being, positive and negative affect).

**Discussion:**

This trial aims to test the effects of an app-based Christian and Islamic meditation, compared to secular mindfulness and a waitlist, using a randomised controlled trial. If the results yield positive outcomes, this study will support the efficacy of these contemplations, offering practitioners a way to enhance their well-being within their religious framework.

**Trial registration:**

ClinicalTrials.gov, NCT06136676. Registered on 18 November 2023.

https://clinicaltrials.gov/study/NCT06136676.

## Background and rationale

Contemplative practices have gained significant popularity since the 1970s [1, 2]. Mindfulness meditation has found a place among therapeutic settings, where practitioners employ it as a strategy to promote wellbeing [3, 4]. Derived from Buddhist and Hindu traditions, mindfulness and Transcendental Meditation are, by far, the most widely researched techniques of contemplative practices [1], with evidence suggesting that its practice can help improve mental health [5, 6], attention [7, 8], and pain management [1, 9]. However, the field of contemplative studies has overwhelmingly used secularised adaptations of meditation practices [1]. Recent criticisms of the present ‘monoculture of mindfulness’ in contemplative science remind us of the extraordinary diversity of such practices across religious traditions, which remains largely unstudied [1, 10, 11]. 

While the focus of therapeutic meditation techniques has been on the reduction of stress generated by postindustrial life [12], religious meditation strives primarily for a deep transformation of the self, where ordinary and self-oriented concerns are replaced by spiritual and prosocial oriented goals [13–15]. Although there is a large body of research that consistently shows positive outcomes of religious practice on health and well-being [16], surprisingly, there has been little interest in studying the effects of religious forms of meditation.

Another gap in the curent contemplative science literature is the study of prosocial effects. Given that these techniques were originally intended to motivate individuals to shift their self-serving interests towards spiritual and other-centred aims, the potential prosocial effects of these practices ought to be more consistently studied. Despite the growth of such studies focusing on mindfulness, loving-kindness, and compassion meditation [17–19], this research has rarely addressed traditional meditation practices, although there has been limited research into the effects of Christian prayer on prosociality tendencies [20], charitable giving [21], and the cultivation of forgiveness and empathy [22, 23]. 

Within Christian and Islamic traditions, which are the two largest Abrahamic religions worldwide, contemplative practices often seek to induce strong emotions, such as joy, love, and repentance, while engaging in recitation, visualisation, and breathing, with the aims of perfecting oneself and deepening one’s relationship with God [24–27]. Such an approach contrasts with mindfulness meditation, which seeks to attain states of calmness through techniques designed to mitigate emotional reactivity [28]. 

One important aspect that is common to Christianity and Islam is the symbolic role played by the heart [29], as evidenced by its scriptures [30–32] and contemplative practices [33–35]. There are various Christian and Islamic meditation practices that attribute particular attention to the heart. For example, in the Christian Sacred Heart of Jesus practice, individuals contemplate the sacred heart of Jesus through visualisation alongside prayer recitation. Devotion to Jesus’ heart directs an individual’s heart towards receiving and reciprocating Jesus’ love [27, 33]. In Islam, The Brilliance of Hearts meditation combines visualisation exercises with prayer recitation and strong emotional emphasis on the expression of love for God [26, 34]. Despite their particularities and varieties of expression, both traditions share elements at the technical level (heart focus), in aim (closeness to God and transforming the self), and in stimulating strong emotions (e.g. devotion, repentance, love). While there is growing evidence showing the positive effects of Christian (and, to a lesser extent, Islamic) religious practices on physical and mental health, such as reducing stress [36, 37], pain [38], and cardiovascular risk [39], the experimental evidence on the salutary effects of Christian and Islamic contemplation techniques is extremetly limited.

Given the plethora of studies on the effects of mindfulness meditation, on the one hand, and the extremely limited literature on Christian and Islamic meditation, this study proposes a mixed methods approach to understanding how these latter traditional forms of meditation might impact individuals. Hence, the study includes psychophysiology, cognition, social functioning, and mental health outcomes. In addition, because of the spiritual aims of these practices, which are expected to effect changes in how one perceives oneself and behaves towards others, the study also includes measures of religiosity. The choice of variables to study was guided both by the current state of the meditation literature (for a summary, see Oman [1]) and by the particular characteristics and aims of Christian and Islamic contemplative practices.

## Research question and hypotheses

This study addresses the effects of heart-centred meditation from the Christian and Islamic traditions, compared to secular practices, on social functioning, physiology, cognition, and mental health. The key question is whether the regular practice of Christian or Islamic heart-centred contemplation fosters positive outcomes at the interpersonal and the individual levels, as compared to a standardised mindfulness-based stress reduction intervention (MBSR) and a waitlist control condition.

To address these questions, this study will develop (a) an 8-week intervention based on heart-centered Christian and Islamic contemplative practices; (b) a stratified 3-arm randomised controlled trial (RCT) with contemplations (Christian and Islamic), an active control (MBSR) and a waitlist control. The contemplation and MBSR programs will be delivered through a mobile app.

We hypothesise that when compared to baseline, individuals undertaking the heart-centred contemplative practices will show: (1) greater prosociality, forgiveness, empathy, and perspective taking; (2) increased pain tolerance and attention, and reduced subjective ratings of pain intensity, reduced stress reactivity as measured by HR and HRV, and reduced psychophysiological reactivity associated with forgiveness as measured by HR and HRV; (3) reduced self-reported stress, depression, anxiety; (4) increased subjective wellbeing and positive affect as well as reduced negative affect. We also hypothesise that these outcomes will be greater for participants in the heart-centred contemplations compared to those in the waitlist control condition. We have no specific predictions for comparing the outcome of the religious (Christian or Islamic) *versus* MBSR interventions.

### Methods

#### Trial design

The study employs the Standard Protocol Items Recommendations for Interventional Trials (SPIRIT) [40] as the reporting guideline for this protocol and adheres to Consolidated Standards of Reporting Trials (CONSORT) [41] to ensure quality in study planning, implementation, and reporting.

Figure 1 and Table 1 show the study procedure and the setup of the randomised control trial. This is a 3-arm stratified randomised controlled trial, with four groups distributed across two variants of the spiritual meditation condition (Christian and Islamic), MBSR, and a waitlist control condition. Participants will be first stratified into Christian and Muslim samples and then randomly allocated to one of the three conditions. Individuals assigned to the spiritual meditation condition will be further stratified into either a Christian or an Islamic contemplation subgroup within the spiritual meditation condition based on their religious affiliations.

Participants in the spiritual meditation groups and the secular mindfulness group will receive 8-week interventions, commencing with an initial face-to-face meeting, where they will practice the first session of the guided meditation course using the mobile app. Following that, they will continue with daily guided practices lasting approximately 20 min through the app. Assessment will be held at three time points including pre-intervention (T1, baseline), after the 8-week intervention (T2), and three months after the intervention (T3). Participants in the waitlist control group will only attend the assessments at T1 and T2, as due to ethical reasons they will be given the option to start using the Christian or Islamic meditation App after testing at T2.

**Fig. 1 Fig1:**
[figure not shown]
Flowchart of the study procedures

**Table 1 Tab1:**
[figure not shown]
Schedule of enrolment, interventions, and assessments

## Setting

The pilot study took place in the lab at Coventry University, in England. The main trial will be conducted at two university Colleges in the state of Kerala, India, where there are large Christian and Muslim populations who are proficient in English. Two designated rooms at each College will be used as laboratories for data collection.

## Participants

### Power analysis

This study will recruit non-clinical samples of 144 Christian and 144 Islamic healthy adult participants. An a priori power analysis was conducted using the G*Power software (V.3.1) [42], considering four groups with mixed method repeated measures at three timepoints. The calculation was conducted based on a small effect size of *f*^*2*^ = 0.1, with an alpha value of 0.05, a desired power of β = 0.85. Effect size was set at 0.1 using a conservative approach due to the novel nature of the study to examine the effects of Christian and Islamic contemplation. Calculation was applied to determine the total sample size of 288 participants with (*n* = 72) per group, after adjusting for an estimated dropout rate of 10%.

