### Study interventions

The spiritual meditation interventions and MBSR will have the same structure and time frame. All interventions will be delivered through an initial face-to-face meeting, where participants will initiate the first session of the guided meditation course using the mobile app. Subsequently, they will continue with daily guided practices lasting approximately 20 min through the app over eight weeks. The initial meeting will start at the end of the baseline assessment (T1). Participants will only be able to access the app intervention that they are allocated to. Participants in the waitlist control group will not receive any types of intervention and will not attend the T3 assessment, but they will be given access to the Christian or Islamic meditation app version upon completion of the in-person T2 assessment.

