### Analysis plan

#### Quantitative data

The analyses will follow both intention-to-treat principle and per-protocol principle, requiring a minimum completion of four days of meditation sessions per week over the 8-week intervention period and complete all required assessments. This study will consider a result with a p-value lower than 0.05 as statistically significant. A series of mixed-design Repeated Measures Multivariate Analysis of Variance (RM-MANOVA) will be used to test the mean difference in the outcomes among conditions (Spiritual meditation, mindfulness, and waitlist control groups) across T1, T2 and T3 as well as within participants across all time points (T1, T2 and T3). The specific prosociality variable, measured by Charitable Giving task, will be only compared between groups at T2. When justifiable, missing data will be imputed using multiple imputation of chained equations [68]. 

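### The stated 85% power belongs to a four-group, three-time-point test that no primary outcome has, and the printed effect size (f² = 0.1) does not give 288; the shortfall is modest except for Charitable Giving

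*Protocol article*

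**What the plan says.** The Power analysis section plans 288 participants, 144 per religion and 72 in each of four groups. The G*Power calculation was done "considering four groups with mixed method repeated measures at three timepoints". It was "based on a small effect size of *f*^*2*^ = 0.1", "with an alpha value of 0.05" and "a desired power of β = 0.85", and the total was then adjusted for 10% dropout. The effect is given again without the square: "Effect size was set at 0.1 using a conservative approach". No correlation among repeated measures is given.

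Elsewhere the article sets out a different layout:

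- **Visits.** Table 2 and the Primary outcomes section place the Dictator Game, Social Value Orientation, forgiveness and empathy at T1 and T2. Only Perspective Taking is measured at T1, T2 and T3.
- **Charitable Giving.** From the Quantitative data section: "The specific prosociality variable, measured by Charitable Giving task, will be only compared between groups at T2".
- **Waitlist.** The Study interventions section says that these participants "will not attend the T3 assessment".
- **Comparison.** The Quantitative data section compares three conditions (spiritual meditation, mindfulness, waitlist).
- **Hypotheses.** The only directional between-arm prediction is spiritual meditation against waitlist.

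**The concern.** There are two separate faults. First, f² = 0.1 means f = 0.316, which fits neither the description of the effect as small nor a sample of 288. A reader who takes the figure literally would think the trial was sized for an effect far larger than the one actually used. Second, the 85% describes a test of four groups over three visits. Dropping a visit, merging groups or using a single post-treatment measurement changes both the noncentrality and the degrees of freedom, so the 85% does not carry over.

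Readers will use the power statement to judge null results. A null on Charitable Giving, one of six primary measures, would be set against a claimed 85% that was never calculated for it.

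**Working it through.** **Inputs from the article.** Alpha 0.05, power 0.85, k = 4 groups and m = 3 time points in the calculation, 10% dropout, N = 288. Completers: 288 × 0.9 = 259. With 72 per group, the spiritual arm has 144 × 0.9 ≈ 130 completers and the waitlist 72 × 0.9 ≈ 65.

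**Assumptions, not in the article.** The tested effect is the group-by-time interaction; sphericity holds; the correlation ρ between repeated measures is 0.5, varied from 0.3 to 0.7.

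**Formula.** Noncentral F with λ = N·m·f²/(1 − ρ), df1 = (k − 1)(m − 1), df2 = (N − k)(m − 1).

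**Step 1: reproduce 288.** With k = 4, m = 3, f = 0.10 and ρ = 0.5, the smallest N with power of at least 0.85 is 258: λ = 258 × 3 × 0.01/0.5 = 15.48, df 6 and 508, power 0.851. Then 258/0.9 = 286.7, so 287, and the next multiple of four is 288 = 4 × 72. The plan's figure is recovered.

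**Step 2: use the effect as printed.** With f² = 0.1 and everything else the same, N = 29 (32 in equal groups, 36 enrolled after dropout). With 259 completers the power would exceed 0.99. Other test families with f² = 0.1 (within, between, multivariate; two or three time points; three or four groups) gave at most about 130 before dropout. The value used was therefore f = 0.10, that is f² = 0.01, one tenth of the printed f².

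**Step 3: power for the layouts in the plan**, at f = 0.10 with 10% dropout:

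| Test | Completers | ρ = 0.3 | ρ = 0.5 | ρ = 0.7 |
|---|---|---|---|---|
| Stated: 4 groups × 3 time points | 259 | 0.69 | 0.85 | 0.98 |
| 3 conditions × 2 time points | 259 | 0.68 | 0.825 | 0.97 |
| Spiritual v waitlist, T1–T2 | 195 | 0.65 | 0.79 | 0.95 |
| Charitable Giving, T2, 3 conditions | 259 | 0.28 | 0.28 | 0.28 |
| Charitable Giving, T2, 4 groups | 259 | 0.24 | 0.24 | 0.24 |

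At ρ = 0.5:

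- Three conditions × two time points: λ = 259 × 2 × 0.01/0.5 = 10.36, df 2 and 256.
- Spiritual versus waitlist: λ = 195 × 2 × 0.01/0.5 = 7.8, df 1 and 193.
- Charitable Giving is a one-way comparison with λ = N·f² = 259 × 0.01 = 2.59, df 2 and 256 (three conditions) or 3 and 255 (four groups). It does not involve ρ.

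Perspective Taking over T1–T3 can be compared only without the waitlist. With 216 × 0.9 ≈ 194 completers in two conditions, power is 0.87 at ρ = 0.5, but this is not the comparison with the waitlist that the hypotheses name.

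**The case against.** The defence is strong on impact. The squared symbol is almost certainly a labelling slip: the article calls the effect small, repeats 0.1 without the square, and 288 reproduces with f = 0.10. For the planned three-condition analysis at two time points, the loss at ρ = 0.5 is only from 0.853 to 0.825. If all 288 are analysed, as intention-to-treat with imputation might allow, power is 0.866. At ρ = 0.7 it is 0.97, well above 0.85. All of this stands, and it limits the size of the point. It does not make the printed effect size right, and it does not help Charitable Giving, where even 288 completers give only 0.31 with three conditions.

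Three stronger readings are tempting but not supported:

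- **The trial is badly underpowered throughout.** A reader might infer this from the 0.68 at ρ = 0.3. The protocol's own layout falls to 0.69 there, so nearly all of that drop comes from the correlation and not from the layout.
- **Spiritual versus waitlist is severely underpowered.** At the planned f = 0.10 with groups in a 2:1 ratio, power is about 0.79 at ρ = 0.5. Much lower values require a smaller effect than the article states.
- **The group sizes contradict the allocation.** The Trial design section says "Participants will be first stratified into Christian and Muslim samples and then randomly allocated to one of the three conditions", and equal allocation would not give 72 in each group. But equal allocation is stated nowhere, the Randomisation and allocation section also refers to four groups, and 72 per group with 144 per religion already implies 2:1:1 within each religion. An unprinted ratio is detail that an article may leave to the full protocol.

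**Conclusion.** The point holds in a limited form. The effect size is wrong as printed, and the 85% belongs to a test that no primary outcome can supply. N = 288 is itself reproducible and need not be questioned.

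For the two-time-point outcomes the difference due to the layout is about 0.01 to 0.03 in power for three conditions, and about 0.03 to 0.06 for spiritual versus waitlist. Whether power falls below 0.85 depends on a correlation that the article does not give. Only Charitable Giving is far short, at 0.24 to 0.28, and that holds for every correlation because there is a single measurement.

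These figures assume f = 0.10, 10% dropout and sphericity. If f² = 0.1 was truly intended, the repeated-measures tests would have power above 0.99, and the stated 85% would still be wrong.

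**What to change.** Keep N = 288 and rewrite the Power analysis paragraph:

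1. Give the effect size as f = 0.10 (f² = 0.01), and label 0.85 as power (1 − β), not as β.
2. State the tested effect and the assumed correlation and sphericity, with a range for the correlation.
3. Restate power, or the detectable difference, for three conditions over T1–T2, for spiritual meditation versus waitlist at T2, and for Charitable Giving at T2 only.
4. Say plainly that Charitable Giving has low power at f = 0.10, so that a null there is not read against 85%.

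The cost is one paragraph and a less favourable stated power. No participants are added, and neither the conduct nor the analysis of the trial changes.

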## Inclusion and exclusion criteria

Inclusion criteria are: (1) 18 to 60 years old; (2) able to read, speak, and understand English; (3) willing to be assigned to any condition, with religious affiliation limiting allocation to either the Christian or Islamic type of spiritual meditation condition; (4) consider oneself to be a Christian or Muslim and pray at least weekly.

Exclusion criteria are: (1) currently suffering from any mental health conditions or using medication to manage mental health conditions; (2) having long-term serious physical medical problem, such as liver, brain, kidney, or other life-threatening chronic diseases; (3) having a history of a heart condition, high blood pressure, Raynaud syndrome, diabetes, or musculoskeletal condition; (4) the current use of anxiolytics or mood stabilizers [43]. 

## Recruitment, screening, and enrolment

The recruitment process started on 22 July 2024. Non-clinical samples of Christian and Islamic healthy adult participants will be recruited and enrolled from the local institutions through their internal participant pools, online adverts, distributing flyers, and collaboration with religious communities.

Potential participants will be contacted via email with detailed information in a written form and will be required to fill out a pre-screening online questionnaire. Their self-reports will be assessed through inclusion and exclusion criteria to determine their eligibility. The reason for ineligibility will be retained in accordance with CONSORT standards [41]. 

Eligible participants will receive information about the study including its objective and procedures. Subsequently, research team member will ask participants to provide informed consent for study enrolment. All enrolled participants will be invited to take part in the baseline assessment (T1) and the follow-up assessment (T2) with measures of social functioning, physiology, and cognition. A set of online measures concerning mental health, religiosity, socioeconomic status, demographics, social value orientation, and meditation social desirability will be taken at home before T1. Additionally, participants in the religious contemplation groups and MBSR will attend an online 3-month follow up assessment. All participants will be compensated with an INR 2,000 as compensation for their time.

